### Fat-free body mass

2.3

Lean body mass is measured using Harpenden skinfold caliper and Baty body assessment software (Baty International Ltd., UK). Lean body mass is derived from patient's height and weight using 3 site Jackson/Pollock algorithm.^[16]^ The algorithm uses different measuring sites for men and women (the sites for male subjects are: chest, abdominal and thigh, for female subjects are: triceps, suprailiac, and thigh). Fat-free body mass is presented as an absolute value and expressed in kilograms, as well as in relation to body weight and expressed in percentage. The inter- and intra-observer variability is 14.4% and 9.1%, respectively.

### Pulmonary function assessment

2.4

We use Asma-1 (Vitalograph, Ireland) peakflowmeter for assessment of peak expiratory flow (PEF, L/min) and 1 second forced expiratory flow (FEV_1_, L). Test is performed in standing position and we record the highest value out of 3 attempts. Data are presented as actual values and percentages of predicted values. The inter- and intra-observer variability are 9.4% and 7.9%, respectively. There is also a temporal variability up to 19% depending on patient's condition (e.g., patient with chronic obstructive pulmonary diseases).

### Pulse wave velocity for arterial stiffness measurement

2.5

We use pulse wave velocity between carotid and femoral arteries (cfPWV) for assessment of arterial stiffness. For these measurements we use piezoelectric mechanotransducers in carotid and femoral sites (Complior, Alam Medical, France). This methodology is recommended by European Society of Hypertension.^[17]^ The right-sided carotid-femoral distance is measured with Seca mod. 207 height meter (Seca, Germany). Blood pressure is measured in a supine position, after at least 5 minutes of rest using Microlife BP A1 sphygmomanometer immediately before PWV assessment on a dominant arm. Arterial stiffness is expressed in meters per second. We will analyze also derived variables like: central blood pressure, central pulse pressure, and augmentation index. Derivatives are calculated by the software from the carotid pulse waveform. The inter- and intra-observer coefficients of variation are 12.3% and 7.4%, respectively.

### Biomarkers

2.6

Twenty milliliters of fasting blood is drawn for preparation of blood plasma, serum, and peripheral blood mononuclear cells. Samples are frozen at –85 °C until further analysis. All analyses will be done after enrollment of the last patient. We plan to measure following biomarkers: C-reactive protein, tumor necrosis alpha (TNFα), interleukin 6 (IL-6), soluble suppression of tumorigenicity protein (ST2), klotho, galectin3, pregnancy associated plasma protein A (PAPP-A), telomere length and telomerase activity, specific miRNA (e.g., mir-122-5p, miR-126, miR-133, miR-16). Soluble ST2 will be measured using Aspect-Plus ST2 Test (Critical Diagnostics, California, USA). Its sensitivity limit is 12.5 ng/mL, recommended upper reference limit is 35 ng/mL. Total coefficient of variation is 14.2%.

### Study outcomes

2.7

The outcomes are designed to answer the following questions: effectiveness of revascularization, its safety, and the overall health of study population in 36-month long follow-up. We consider effective revascularization as complete supply of blood to all ischemic territories of coronary tree, obtained either percutaneously or surgically. In some cases of multi-vessel coronary heart disease and percutaneous revascularization we allow the revascularization to be performed in staged procedures. In such cases, the effectiveness will be assessed after final procedure. The assessment will be carried out by 2 independent operators by visual evaluation of final angiogram. Any discrepancies in assessment will be resolved by consensus. Any functional or alternative imaging assessments, like intravascular ultrasound, optical coherence tomography, or fractional flow reserve are left for operator's decision and will be added to our records.

In the category of procedural safety we will assess peri-interventional myocardial infarction, contrast induced nephropathy, and bleeding. Periprocedural myocardial infarction is defined according to description provided by Thygesen et al.^[18]^ It is characterized as “elevation of cardiac troponins >5× 99th percentile of upper reference limit occurring within 48 hours of the procedure plus either evidence of prolonged ischemia (20 minutes) as demonstrated by prolonged chest pain, or ischemic ST changes or new pathological Q waves, or angiographic evidence of a flow limiting complication, such as of loss of patency of a side branch, persistent slow-flow or no-reflow, embolization, or imaging evidence of new loss of viable myocardium or new regional wall motion abnormality.”

Contrast induced nephropathy is defined after Parfrey et al^[19]^ as “increase in the serum creatinine concentration of >25%, or of >0.5 mg/dL within 48 hours after the administration of the contrast agent.”

Bleeding is defined after Smith et al^[20]^ as “blood loss at the site of arterial or venous access or due to perforation of a traversed artery or vein requiring transfusion and/or prolonging the hospital stay, and/or causing a drop in hemoglobin >3.0 g/dL. Bleeding attributable to the vascular site could be retroperitoneal, a local hematoma >10 cm diameter or external.” Bleeding from non-access sites like intracranial hemorrhage, gastrointestinal, or genitourinary blood loss will be recorded either to ascertain safety of antiplatelet or anticoagulation treatment in frail patients.

For the assessment of overall patients’ health we will monitor 3-year mortality, either all-cause and cardiovascular, re-infarction, re-intervention, stroke, new-onset heart failure, any hospital readmission, and a combination of all above mentioned. The 36-months long follow-up is based on semi-annual telephone contact with patient or designated family member.

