### Patient population

2.1

The FRAPICA trial is a single center, observational, prospective, study. One thousand patients aged ≥65 years with symptomatic coronary heart disease will be enrolled. Patients with all clinical presentations of coronary artery disease are eligible. Stable coronary heart disease is diagnosed on the base of exercise induced ischemia, resolving after rest. Acute coronary syndrome includes ST segment elevation myocardial infarction, non-ST segment elevation myocardial infarction and clinical presentation of unstable angina. The latter is characterized by myocardial ischemic pain at rest or at minimal physical activity in the absence of myocardial necrosis. Non-ST segment elevation myocardial infarction is diagnosed in patients with symptoms of ischemia, electrocardiographic abnormalities such as ST-segment depression, inversion of T wave, flattened T wave, pseudo-normalization of previously negative T waves, and presence of cardiomyocyte necrosis. ST-segment elevation myocardial infarction is diagnosed when acute precordial pain (>20 minutes), persistent ST-segment elevation, cardiomyocyte necrosis, and typical angiographic findings are present.^[11]^ Either femoral or radial approaches are acceptable—the choice of puncture site depends on patient's or operator's preference and basically on medical conditions. Only patients with type 1 myocardial infarction are considered eligible for the study. Method of revascularization is decided by the operator and ad hoc percutaneous coronary intervention is sometimes performed. Mostly, this is a case in a low-risk patients with single vessel disease, or in cases of ST-elevation myocardial infarction (STEMI) or non ST-elevation myocardial infarction (NSTEMI) patients with identifiable culprit artery. Nevertheless, all coronary angiographies are assessed and discussed by a heart team, selected records are re-consulted with a cardiac surgeon and a further revascularization schedule is planned. For the risk stratification we use Syntax score and logistic Euro score. After performed coronary angiography and confirmation of coronary heart disease with documented significant stenosis, patients are screened and written informed consent is obtained. Protocol of the study was approved by Internal Review Board of Medical University of Silesia. For the purpose of this study we record demographic, clinical, laboratory, angiographic data from patient's medical charts, assess the presence of frailty syndrome, measure arterial stiffness, body composition, pulmonary function, and draw fasting blood for further analyses. Study flowchart is shown in Fig. 1.

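### The periprocedural infarction definition sets no pre-procedure troponin condition, so as written it cannot separate index from procedural infarction in STEMI patients and, in part, in NSTEMI patients

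*Protocol article*

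**What the plan says.** Section 2.7 of the protocol article (Study outcomes) names periprocedural infarction as one of three procedural safety outcomes. It takes the definition from a cited consensus description and quotes the text. The rule needs troponin above five times the 99th "percentile of upper reference limit occurring within 48 hours of the procedure plus either evidence of prolonged ischemia (20 minutes") or another listed sign; one supporting sign is enough. The ischaemia signs are to be judged "as demonstrated by prolonged chest pain, or ischemic ST changes or new pathological Q waves, or angiographic evidence of a flow limiting complication", and imaging evidence of new damage also counts. The word new is attached to the Q waves and to the imaging findings. It is not attached to the chest pain or the ST changes.

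Section 2.1 (Patient population) sets the cohort: "Patients with all clinical presentations of coronary artery disease are eligible". For STEMI the entry rule is: "ST-segment elevation myocardial infarction is diagnosed when acute precordial pain (>20 minutes), persistent ST-segment elevation, cardiomyocyte necrosis, and typical angiographic findings are present". For NSTEMI it begins: "Non-ST segment elevation myocardial infarction is diagnosed in patients with symptoms of ischemia, electrocardiographic abnormalities such as ST-segment depression"; it then lists several T-wave changes and requires necrosis. The same section says that ad hoc PCI is sometimes done, mostly in low-risk single-vessel disease or "in cases of ST-elevation myocardial infarction (STEMI) or non ST-elevation myocardial infarction (NSTEMI) patients with identifiable culprit artery".

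Section 2.10 expects around 100 STEMI patients; section 2.1 gives a total of 1000. The article states no NSTEMI count and no expected rate of periprocedural infarction.

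**The concern.** The troponin component is an absolute level measured around the procedure, not a change from a value before it. The two neighbouring safety outcomes in section 2.7 are framed as change: nephropathy is a rise in creatinine after contrast, and bleeding includes a fall in haemoglobin. Infarction has no such anchor.

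In a STEMI patient treated early, the index troponin elevation falls inside the 48-hour window, and the pain and ST elevation that led to enrolment can serve as the supporting sign. Someone applying the printed rule has no ground for calling this anything other than a periprocedural event.

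The study asks whether frailty predicts outcome, including procedural complications. If the endpoint partly records presentation, two errors are possible. Where presentation is unrelated to frailty, false events are spread evenly and a real association shrinks. Where it is related, an association appears, or is hidden, without any difference in procedural harm.

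**Working it through.** The article gives no rate or power for this endpoint, so there is no figure to reproduce. The check has a logical part and a scenario part.

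**1. Entry rule against endpoint rule**

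| Endpoint component | STEMI at entry | NSTEMI at entry |
|---|---|---|
| Troponin above 5 times the limit | Necrosis required, level not stated | Necrosis required, level not stated |
| Prolonged pain (20 minutes) | Pain over 20 minutes required | Ischaemic symptoms, no duration |
| Ischaemic ST changes | Persistent ST elevation required | ST depression is one option; T-wave changes alone suffice |
| New Q waves, new imaging loss, flow-limiting complication | Not implied | Not implied |

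For STEMI, the supporting sign is met at entry and only the troponin level remains open. For NSTEMI, the overlap is partial.

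**2. Share of counted events that would be false (STEMI only)**

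Inputs: 1000 patients (section 2.1) and about 100 with STEMI (section 2.10). Assumptions: 50% or 100% of STEMI patients meet the printed wording through the index infarct, giving F = 50 or 100 false events; the true periprocedural rate t is 2%, 5% or 10%.

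True events = t × (1000 − F). False share = F / (F + true events).

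| t | F = 50 | F = 100 |
|---|---|---|
| 2% | 50/(50 + 19) = 72% | 100/(100 + 18) = 85% |
| 5% | 50/(50 + 47.5) = 51% | 100/(100 + 45) = 69% |
| 10% | 50/(50 + 95) = 34% | 100/(100 + 90) = 53% |

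**3. Dilution when presentation does not differ by frailty**

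Inputs: 20% frail (the figure cited in the Introduction), so 200 frail and 800 non-frail patients; significance level 0.05, taken as two-sided (section 2.10). Assumption: true rates of 10% and 5%. With a fraction f = F/1000 falsely positive in both groups, the observed rate is f + (1 − f) × true rate. Power uses the normal approximation for two proportions.

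- F = 0: 10.0% v 5.0%, risk ratio 2.00, power 72%.
- F = 50: 14.5% v 9.75%, risk ratio 1.49, power 49%.
- F = 100: 19.0% v 14.5%, risk ratio 1.31, power 36%.

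**4. Confounding when presentation does differ**

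Assumptions: STEMI in 15% of frail and 9% of non-frail patients (200 × 0.15 + 800 × 0.09 = 102 patients, in line with the stated 100), and the same true risk of 5% in both groups.

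- All STEMI patients qualify: frail 0.15 + 0.85 × 0.05 = 19.3%; non-frail 0.09 + 0.91 × 0.05 = 13.6%.
- Half qualify: frail 0.075 + 0.925 × 0.05 = 12.1%; non-frail 0.045 + 0.955 × 0.05 = 9.3%.

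The true difference is zero in both cases.

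**The case against.** The strongest reply is that section 2.7 defers to a source: "Periprocedural myocardial infarction is defined according to description provided by" a cited document that cannot be checked here. That source, or the full protocol behind the article, may hold a baseline rule, and adjudicators may apply it. The Abstract also calls the event procedure-related, which shows the intent. This stands as a limit on the practical effect: with such a rule in use, few index infarcts would be counted. It does not remove the point. The article prints an operative definition without that rule, and nothing else in it adds one or exempts acute infarction from this endpoint.

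Second, the Abstract and section 2.10 plan analyses by clinical presentation, crude or adjusted. These would expose a presentation artefact. They would not make the events counted within the STEMI stratum valid.

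Third, the study is sized on mortality and new-onset heart failure, and the combined long-term outcome as listed in section 2.7 does not include procedural events. That is fair, and it confines the damage mainly to this one safety outcome.

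A reader might also infer that every NSTEMI patient meets the definition through the index event. The entry rule does not support this: it sets no pain duration and no troponin level, and it accepts T-wave changes that the endpoint does not list. Nor does the article show that the PCI-type signs, such as side-branch loss, are meant to be applied to surgical patients. A separate surgical rule is a detail that an article may leave to the full protocol.

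**Conclusion.** The point holds for the definition as printed. It has no pre-procedure troponin condition and accepts pain and ST changes that need not be new, in a cohort that includes STEMI patients who have both by definition. The overlap is close to complete for STEMI and partial, of unknown size, for NSTEMI.

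The endpoint may be substantially inflated. Counting STEMI alone, 34% to 85% of events would be false under the scenarios above. Only the 100 STEMI patients and the total of 1000 come from the article; the true rates and the share of STEMI patients who qualify are assumptions. False events are the majority in five of the six scenarios, not in all. It is therefore tempting to say that the endpoint is swamped by false events, but the article gives no event rate, troponin levels or NSTEMI count from which that could be shown.

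Whether the effect on frailty is dilution or confounding depends on whether presentation differs by frailty, which the article does not say.

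**What to change.** Amend the wording in section 2.7 and the adjudication instructions before analysis:

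- Require a normal pre-procedure troponin, or a stable or falling one followed by a renewed rise after the procedure.
- Require the ischaemic symptoms or ECG changes to be new and to arise after the procedure.
- Treat the endpoint as not evaluable in acute infarction with troponin still rising at the time of the procedure.
- Report the endpoint by clinical presentation, with the number evaluable in each group.

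If the cited source or the full protocol already holds a baseline rule, printing it in section 2.7 may meet the first item; the others still need to be checked against it.

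The change touches endpoint wording and event classification only. The cost is a smaller evaluable set, and so less precision, for this one endpoint. It also relies on serial troponins being in the medical charts. The article says that laboratory data are taken from the charts but does not say that troponin was measured both before and after every procedure.

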## Introduction

1

Frailty gains growing attention of clinical research community as society of developed countries and their cardiovascular patients are aging. Frailty syndrome is characterized by reduced physiological reserve and increased susceptibility to various stressors.^[1]^ Several diseases, either acute or chronic, or iatrogenic circumstances may act as stressors. Frail patients, after being exposed to such stressors, may react with incommensurate decompensation, and adverse outcomes. They are at higher risk of procedural complications, long-lasting recovery, functional deterioration, physical disablement, and increased risk of death.^[2]^ The syndrome is frequently associated with comorbidities.^[3]^ Symptomatic coronary heart disease, either stable or unstable, is the prevailing disease unit among elderly patients. Inversely, data on prevalence of phenotype frailty among patients aged ≥65, who underwent percutaneous coronary angioplasty were recently published.^[4]^ Gharacholou et al^[4]^ reported that approximately 20% of those patients is frail. Moreover, frail patients have greater comorbid burden and greater angiographic coronary artery disease intensity. However, commonly used risk stratification scales, like Syntax,^[5]^ Euro,^[6,7]^ or GRACE^[8]^ use patient's age as a major determinant of risk, but they do not incorporate the frailty traits into the risk assessment. Technical development has allowed more patients to become eligible for interventional treatment.^[9,10]^ As medical innovations are cost consuming, the individual benefits of such medical procedures are not well defined in particular patient populations. Thus, we need to operationalize more detailed patient selection.

The objectives of the study are to report Fried frailty scale and instrumental activities of daily living (IADL) scale dispersion before hospital discharge and to assess the predictive impact of both scores in a population of elderly patients with symptomatic coronary artery disease.

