## Discussion

4

We do hope that FRAPICA trial with its prospective, observational design, and control of many variables will clarify several issues and the results will be readily transferable for clinical practice. We use 2 different tools for frailty assessment: Fried frailty scale requires accessory equipment (hand dynamometer, stopwatch, computer for leisure time activity calculation) for patient evaluation, while IADL score is ready for use equipment-free assessing tool. Each of the tools will be used for risk stratification separately and in combination. Their predictive value will be compared at the same time. Apart from these scales, we have several additional variables which will be used for supplementary characteristics of frail elderly patients and will be integrated into risk stratification model enabling decision making in this population of patients. The clinical data which we assume may prove important for risk assessment would be evaluated routinely as an evidence-based daily clinical practice. To our knowledge there are only few previous publications dealing with results of interventional treatment.^[4,29]^ The researchers from Mayo Clinic have used the same Fried phenotype frailty assessment tool, but have limited the study population to elderly patients who underwent percutaneous coronary intervention. We aim to analyze 2 other patients’ populations either: this treated surgically and this treated medically.

Complimentary measures of cardiovascular status and body composition will be helpful in better characterization of frailty. Arterial stiffness is more and more often distinguished as a measure of cardiovascular status.^[30]^ It may precipitate symptoms of angina with insignificant lesions within coronary arteries, or it may lead to occurrence of diastolic heart failure in elderly patients.^[31]^ Measurement of arterial stiffness, as a simple and a non-invasive method, can be easily applied at patient's bedside.^[30]^ Of note, increased pulse wave velocity in elderly patients indicates increased risk of adverse cardiovascular outcomes.^[32]^

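### Any readmission, and so the composite, takes in revascularisation already scheduled at the index admission, and re-intervention is not defined to exclude it

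*Protocol article*

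**What the plan says.** Three parts of the protocol article bear on this.

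- **Outcomes.** The Study outcomes section (2.7) gives the 36-month events as "3-year mortality, either all-cause and cardiovascular, re-infarction, re-intervention, stroke, new-onset heart failure, any hospital readmission, and a combination of all above mentioned". Readmission carries no restriction to unplanned admissions. Re-intervention has no definition.
- **Scheduled later procedures.** The same section says "In some cases of multi-vessel coronary heart disease and percutaneous revascularization we allow the revascularization to be performed in staged procedures". The Patient population section (2.1) says that, after heart-team discussion, "a further revascularization schedule is planned". The Discussion adds that the study also covers two further groups, "this treated surgically and this treated medically".
- **How stages are treated elsewhere.** For the effectiveness outcome, staged patients are handled as one course of treatment: "the effectiveness will be assessed after final procedure". The article does not carry this rule over to the follow-up events.

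The frailty scales are recorded before discharge (Introduction). A stage done at a later admission therefore falls after baseline. The Statistical analysis section (2.10) plans Kaplan–Meier and Cox analyses of the outcomes.

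**The concern.** One and the same procedure is the completion of treatment under the effectiveness outcome and, through readmission, an adverse event under the follow-up outcomes. A scheduled return typically comes early. If the composite is analysed as time to first event, that return ends the patient's contribution to it, and a later death or infarction no longer counts there.

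The study's purpose is to measure how well frailty predicts outcome. Whether a patient is staged depends on the extent of disease and on the treatment chosen, and neither need be independent of frailty. The Introduction reports from a cited study that "frail patients have greater comorbid burden and greater angiographic coronary artery disease intensity". A tendency to treat frail patients less would push the other way. So the composite and readmission results would partly describe treatment scheduling, with a bias whose direction cannot be known in advance.

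**Working it through.** **What can be reproduced.** Nothing on this point. Section 2.10 gives expected event numbers for deaths (about 100) and new-onset heart failure (at least 45), but none for the composite, readmission or re-intervention. No staging proportion is given either.

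**Inputs from the article.** 1000 patients; about 20% frail (Introduction, from a cited cohort), so about 200 frail and 800 not frail; 36 months of follow-up; significance at 0.05, read as two-sided.

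**Assumed inputs.** Unplanned composite events are exponential at 15, 30 or 50% per year in non-frail patients, multiplied by the true hazard ratio (HR) in frail patients. Planned returns occur uniformly between 0.05 and 0.25 years, in 5 to 30% of patients. The composite is time to first event, censored at 3 years, with one Cox term for frailty.

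**Check by hand at 15% per year, true HR 1.5.** The unplanned 36-month risk is 1 − exp(−0.45) = 0.362 in non-frail and 1 − exp(−0.675) = 0.491 in frail patients, a risk ratio of 1.35. If a proportion s also has a planned return, the risk becomes 1 − (1 − p)(1 − s).

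- 20% staged in both groups: 1 − 0.638 × 0.80 = 0.490 and 1 − 0.509 × 0.80 = 0.593, ratio 1.21.
- 10% of frail and 25% of non-frail staged: 1 − 0.638 × 0.75 = 0.522 and 1 − 0.509 × 0.90 = 0.542, ratio 1.04.

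**Cox HR by simulation.** Separate runs of the same scenario differed by up to about 0.03.

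| True HR | Events per year | Staged, frail / non-frail | Observed HR |
|---|---|---|---|
| 1.5 | 15% | 5% / 5% | 1.43 |
| 1.5 | 15% | 10% / 10% | 1.39 |
| 1.5 | 15% | 20% / 20% | 1.30 |
| 1.5 | 30% | 20% / 20% | 1.35 |
| 1.5 | 50% | 10% / 10% | 1.43 |
| 1.5 | 15% | 5% / 10% | 1.26 |
| 1.5 | 15% | 10% / 25% | 0.97 |
| 1.5 | 30% | 10% / 25% | 1.10 |
| 1.5 | 50% | 10% / 25% | 1.17 |
| 1.5 | 15% | 30% / 20% | 1.52 |
| 1.0 | 15% | 20% / 20% | 1.0 |
| 1.0 | 15% | 30% / 20% | 1.26 |
| 1.0 | 15% | 10% / 25% | 0.70 |

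Planned returns are about 11% of first composite events at 10% staging and 50% events per year. At 15% per year they are 12% with 5% staging, 22% with 10%, and 38 to 43% in the 20% / 20%, 30% / 20% and 10% / 25% scenarios.

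**Power under equal staging.** Assume a 36-month unplanned risk of 30% in non-frail patients and a true HR of 1.5, so 1 − 0.7^1.5 = 41.4% in frail patients. Comparing these proportions in 200 and 800 patients gives 86% power. With 15% staged in both groups the risks become 1 − 0.700 × 0.85 = 40.5% and 1 − 0.586 × 0.85 = 50.2%, and power falls to 70%. With 30% staged in both it falls to 53%.

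**The case against.** The case for leaving this alone has several parts.

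- **Definitions may sit elsewhere.** The outcomes are one condensed sentence in an article, and planned/unplanned coding is commonly left to a fuller document. That stands for re-intervention, where the article is merely silent. It does not stand for readmission, where the article states that any readmission counts.
- **Stages as re-interventions.** A reader might infer that the article counts stages as re-interventions. It does not say so, and its effectiveness rule leans the other way. Stages done within the index stay are not readmissions either. The point rests on readmission and on the composite that contains it.
- **Size.** Every rate above is assumed, and staging applies only to some multi-vessel cases. That stands: with 5 to 10% staged equally, a true 1.5 is still seen as 1.39 to 1.43.
- **Direction.** The one relevant statement in the article, on disease extent, suggests more staging in frail patients, if anything. At 30% against 20%, a true 1.5 is hardly moved (1.52). Masking needs clearly less staging in frail patients, for which the article gives no evidence.
- **Reversal.** A reader might infer that a true frailty effect could be reversed. An HR of 0.81 does appear with 10% of frail against 30% of non-frail patients staged and a 36-month event risk of 30%; it is 0.95 when that risk is 50%. Nothing in the article supports such a threefold gap, so reversal is not claimed.
- **Unfinished staging.** A reader might also infer that patients who never complete their stages have no effectiveness result. The article does not say this; their last angiogram can be scored as incomplete.
- **Consequence.** The composite is not named as primary, and deaths and infarctions remain in their own analyses. That stands.

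**Conclusion.** The concern holds for any readmission and for the composite; for re-intervention it is a missing exclusion. Followed literally, the text turns revascularisation scheduled at the index admission into an outcome event, while the effectiveness rule in the same section treats it as part of one treatment course.

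Equal staging dilutes a frailty effect and creates none. Unequal staging can mask an effect or create one. Across the scenarios tabulated, a true HR of 1.5 is observed as about 0.97 to 1.52; at 15% events per year, a true HR of 1.0 is observed as about 0.7 to 1.26. These are illustrations, not bounds: they rest on assumed staging proportions, event rates and return times, and on analysing the composite as time to first event. Death, re-infarction, stroke and new-onset heart failure analysed singly are unaffected.

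**What to change.** 1. State in section 2.7 that procedures and admissions scheduled at the index heart-team review are not readmission, re-intervention or composite events.
2. Record a planned/unplanned flag prospectively from the heart-team decision. Follow-up is by telephone every six months, so the flag should not depend on what the patient or a relative recalls.
3. Analyse unplanned readmission, unplanned re-intervention and a composite built from them. Keep the version with all readmissions as a sensitivity analysis.
4. Report the proportion with scheduled later procedures by frailty group, so that readers can judge how far the two versions could differ.

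Removing readmission from the composite altogether is not needed for this purpose. The cost is a small coding task and fewer composite events. The events lost are the scheduled ones, which carry no prognostic information about frailty.
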